## Methods: Data collection and management

Data collection on admission will include the following: demographic characteristics, comorbidities, source of infection, Sequential Organ Failure Assessment at ICU admission, temperature, hemogram lactate, hepatic and renal markers, Glasgow Coma scale or Richmond Agitation Sedation Scale, Confusion Assessment Method for the ICU scale, drug for sedation, neuromuscular blocking agents, mechanical ventilation, quantify vasoactive drug dose on collection day, arterial blood gasses before and after the protocol, presence of acute cardiac dysfunction by echocardiography and left ventricle ejection fraction. We will describe the utilization of antipsychotics or sleep-improving medications before ICU admission.

At the time of data collection, the presence of brain dysfunction associated with sepsis will be assessed by: a Glasgow scale score < 15 or when disorientation, disorganized thinking, or agitation are reported by the attending physician, regardless of sedative/analgesic use and in the absence of neurological disease (i.e., dementia, cerebrovascular disease, brain tumors, previous traumatic brain injury). Data from medical records will be used to access such information, the description of the change in the level of consciousness or the use of antipsychotics or dexmedetomidine will be interpreted as a brain dysfunction.

Systemic physiological monitoring will be performed by an arterial line, cardioscopy, pulse oximetry, and capnography (if unavailable at the time of collection, this will be described). Before starting the monitoring, the proper functioning of the arterial line will be confirmed and the site described.

Each patient will adhere to a uniform protocol where, after establishing baseline measures, the mean arterial pressure (MAP) targets will be sequentially increased in the order of 65, 75, and then 85 mmHg. This structured approach ensures sample homogeneity.

CA assessment by TCD will use a 2 MHz probe, supported by a helmet frame, the middle cerebral artery will be located through the window of the temporal bone, then it will be confirmed by depth and waveform, and one of the sides will be chosen and will be kept during the protocol. All hemodynamic parameters will be collected simultaneously and transmitted to the Doppler Box through a cable connected to the multiparameter monitor. A B4C sensor will be placed on the contralateral temporal window, which consists of a monitor that quantifies local cranial bone deformations using strain-gauge sensors. The system will be positioned on the frontotemporal region, approximately 3 cm over the first third of the orbitomeatal line, and the software will indicate the wave quality generated. The measurement of ICC will be done using the curve generated by B4C, and P2/P1 > 1 will be considered altered. The quality of measurements will be closely monitored during the duration of recordings to ascertain their acceptability for subsequent stages of off-line analysis.

The instantaneous relationship between arterial blood pressure and CBv will be used to estimate CrCP and RAP for each cardiac cycle using the first harmonic method [18]. Beat-to-beat data will be spline interpolated and resampled at 5 Hz to produce signals with a uniform time base.

Dynamic CA will be assessed using transfer function analysis, using spontaneous fluctuations of MAP as input and corresponding changes in CBv as output in recordings for each MAP target (lasting 5 min), as described previously [19,20]. The Welch method will be adopted for smoothing spectral estimates obtained with the fast Fourier transform (102.4 s segments, 50% superposition) leading to frequency-dependent estimates of coherence, gain and phase. Using the inverse fast Fourier transform, the CBv response to a step change in MAP will also be derived and compared with ten template curves proposed by Tiecks et al. [21] to estimate the ARI [22,23] Baseline cerebral hemodynamic parameters will be reported as the average over a 5-min recording at rest. Values of ARI < 4 will characterize impaired dCA.

The protocol will be interrupted if at any time during the data collection any of the adverse effects, described below, are identified.

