#### Selection criteria

Study enrollment will include patients experiencing septic shock for up to 48 hours and still necessitating vasopressor support. Detailed inclusion and exclusion criteria are provided in Table 1.

**Table 1 pone.0304412.t001:** Selection criteria.

Inclusion criteria	Exclusion criteria
• Age > 18	• No temporal window for TCD
• Septic shock < 48h • The timing will be counted from ICU admission or the start of noradrenaline infusion for patients already in critical care units.	• Hepatic or uremic encephalopathy
	• Pregnancy
	• Acute or prior neurological insult*
	• Exogenous intoxication
	• Dementia**
	• Severe hypercapnia*** • Instability for acute arrhythmia
	• Extracorporeal support device by modifying the pulse waveform****
	• Extreme severity, with imminent risk of death

* Ischemic or hemorrhagic stroke, aneurysm, arteriovenous malformation, hydrocephalus, neurological surgery, central nervous system infection.

** Reported or written in medical records.

*** Partial pressure of arterial carbon dioxide (PaCO2) > 65mmHg.

**** Intra-aortic balloon pump (IABP) and Extracorporeal membrane oxygenation (ECMO).

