### Study outcome

The primary endpoint is to assess the impact of different MAP targets on cerebral hemodynamics (ARI, CrCP, RAP by TCD, and P2/P1 by B4C) in patients with septic shock.

Secondary objectives: (1) Evaluate the effects of targeting a MAP of 65 mmHg on cerebral hemodynamics in patients with septic shock. (2) Evaluate the correlation between ARI and B4C. (3) Correlate criteria of clinical severity and neurological dysfunction with cerebral hemodynamics (This will involve assessing the correlation between markers of organ dysfunction such as lactate levels, usage of vasoactive drugs, Sequential Organ Failure Assessment (SOFA) score, and delirium with CA). (4) Assess 28-day mortality.

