### Recruitment

The recruitment phase is set from July 2023 to June 2025. Table 2 details the project’s steps. Septic shock patients starting on noradrenaline, whether newly admitted to or already in the ICU, are potential candidates. However, if an alternative diagnosis emerges within 48 hours, they will be removed from the candidate pool. The multiprofessional team will daily inform the research group about new vasopressor requirements, ensuring rigorous monitoring.

**Table 2 pone.0304412.t002:** Protocol chronology.

		STUDY PERIOD					
	Recruitment	Allocation	Intervention protocol (5 min on each MAP target)			Clinical outcome	
	*07/23–06/25*	*< 48 hours ICU admission*	*MAP 65 mmHg*	*MAP 75 mmHg*	*MAP 85 mmHg*	*7*^*th*^ *day*	*28*^*th*^ *day*

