** *ASSESSMENTS* **							
**Sex, age, time, time since admission to the ICU, infection site, comorbidities, APACHE, SOFA, vasopressor dosage, blood analysis**		x					
**TCD: ARI, CrCP, RAP**			X	X	X		
**B4C: P2/P1 ratio**			X	X	X		
**Brain dysfunction**		X				x	x
**Ventilation free days**							x

MAP: Mean arterial pressure, MCA: Middle cerebral artery, TCD: Transcranial doppler, B4C: Brain4care, ICU: Intensive care unit, APACHE: Acute Physiologic and Chronic Health Evaluation, SOFA: Sequential Organ Failure Assessment, ARI: Autoregulation index CrCP: Critical closing pressure, RAP: Resistance-area product.

The locals researchers will be designated for daily data collection and interactions with patients or their families after the, ensuring that recruitment is possible within 48 hours from the onset of vasopressor therapy to optimize data gathering.

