## Statistical methods: Outcomes

Data will be assessed for normality using the Kolmogorov–Smirnov test. Categorical variables will be compared using the Fisher exact test or chi-square test, as appropriate, and the Student t-test or the Mann–Whitney U-test will be used to compare continuous variables, as appropriate The results will be expressed as the average and standard deviation for normally distributed data, or as the median and interquartile ranges (IQRs) for non-normally distributed data.

The primary outcome will be evaluated at T0 (basal), T1 (65 mmHg), T2 (75 mmHg), and T3 (85 mmHg) using a two-way repeated-measures ANOVA. Due to the longitudinal study design and the dependence between repeated measures, mixed-effects regression models will be considered to develop a model with different pressure targets. Each component of cerebral hemodynamics (ARI, RAP, CrCP, and P1/P2) will be assessed individually. At the 65 mmHg MAP target, cerebral hemodynamics will be evaluated by mean and IQRs.

All secondary outcomes will be exploratory and analyzed using independent samples t-tests, and chi-square test, as appropriate, without additional adjustment. Linear regression, Pearson’s correlation coefficient or Sperman coefficient will be used to test for association between cerebral parameters and organ dysfunction. Statistical analyses will be performed using the last version of SPSS for Windows (Chicago, USA). A p-value<0.05 will be considered statistically significant.

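### SOFA is timed at ICU admission, so for patients whose shock begins later in the ICU the score used in the exploratory severity–autoregulation correlation may predate the shock

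*Protocol article*

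**What the plan says.** Methods: Data collection and management gives SOFA its own time point: "Data collection on admission will include the following: demographic characteristics, comorbidities, source of infection, Sequential Organ Failure Assessment at ICU admission". The same sentence ties vasoactive dose to the day of collection and blood gases to before and after the protocol. The next paragraph assesses sepsis-associated brain dysfunction when the data are collected.

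Eligibility is not tied to ICU admission for everyone. Recruitment states: "Septic shock patients starting on noradrenaline, whether newly admitted to or already in the ICU, are potential candidates". Table 1 sets the clock: "The timing will be counted from ICU admission or the start of noradrenaline infusion for patients already in critical care units".

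Secondary objective 3 (Study outcome) relates "markers of organ dysfunction such as lactate levels, usage of vasoactive drugs, Sequential Organ Failure Assessment (SOFA) score, and delirium with CA". Statistical methods: Outcomes names linear regression and the Pearson or Spearman coefficient for this; in its words, "Sperman coefficient will be used to test for association between cerebral parameters and organ dysfunction".

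Two other places bear on timing. The section on retention and follow-up says data are gathered on one occasion, and excepts only ventilator-free days at day 28 and brain dysfunction at days 7 and 28. Table 2 puts SOFA in a single row, "Sex, age, time, time since admission to the ICU, infection site, comorbidities, APACHE, SOFA, vasopressor dosage, blood analysis", with one mark in the Allocation column, which is headed as under 48 hours from ICU admission.

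**The concern.** A correlation between severity and autoregulation is meant to describe one clinical state. ARI, CrCP, RAP and P2/P1 come from a single session within 48 hours of shock onset, while SOFA as written comes from ICU admission. For someone who develops septic shock during an ICU stay, the two can be separated by days and by the onset of shock itself.

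The stake is an exploratory result, but one that the background section makes of interest, since it cites an inverse relation between ARI and SOFA. If the score is out of date for part of the sample, a weak correlation could reflect timing rather than physiology. The article also says this pilot will inform the sample sizes of later studies, so a distorted estimate could be carried forward.

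**Working it through.** **1. Gap between SOFA and ARI, from the text**

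- Admitted in shock: the clock starts at ICU admission, so the gap is at most about 48 h.
- Already in the ICU: gap = (ICU admission to noradrenaline start) + (up to 48 h). Neither Table 1 nor Recruitment bounds the first term.

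**2. Do other passages settle the timing?**

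| Place | Implied SOFA time |
|---|---|
| Data collection and management | ICU admission, stated explicitly |
| Retention and follow-up | The single collection occasion; SOFA is not an exception |
| Table 2, Allocation column | Within 48 h of ICU admission, in the same row as vasopressor dosage, which the text sets on the collection day |

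These three do not agree. The Table 2 column heading also does not fit a patient whose clock starts at noradrenaline after a longer ICU stay. No passage states a SOFA on the recording day.

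**3. Illustration of the possible loss**

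The article gives no effect size or power to reproduce. From the document: n = 40 (the stated minimum) and significance at 0.05, taken as two-sided. Everything else is assumed.

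Power = Φ(atanh|r| × √(n−3) − 1.96), with √37 = 6.083. The smallest |r| reaching p < 0.05 is tanh(1.96/6.083) = 0.31.

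(a) All patients equally affected: observed r = true r × ρ, where ρ is the correlation of admission SOFA with session SOFA. Assumed true |r| = 0.40.

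| ρ | observed r | atanh(r) × 6.083 | power |
|---|---|---|---|
| 1 (same day) | 0.40 | 2.577 | 0.73 |
| 0.8 | 0.32 | 2.017 | 0.52 |
| 0.6 | 0.24 | 1.489 | 0.32 |

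(b) Only a share s affected, with equal means and variances: observed r = true r × [(1−s) + sρ].

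- s = 25%, ρ = 0.5: 0.40 × (0.75 + 0.125) = 0.35, power 0.60. For ρ from 0.3 to 0.9, power is 0.55 to 0.71.
- s = 50%, ρ = 0.5: 0.40 × (0.50 + 0.25) = 0.30, power 0.47. For ρ from 0.3 to 0.9, power is 0.37 to 0.68.

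**4. Is the direction certain?**

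Suppose a share p of patients are ICU-onset. Their admission SOFA is 1 SD low and correlates 0.40 with the session score, against 0.85 in the others. Their mean ARI differs by d SD. With true r = −0.40:

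r = {−0.40 × [0.85(1−p) + 0.40p] − p(1−p)d} / √{[1 + p(1−p)] × [1 + p(1−p)d²]}

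With p = 0 this gives −0.34. With p = 0.20 the first term of the numerator is −0.304 and p(1−p) = 0.16:

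| d | r |
|---|---|
| −0.5 | (−0.304 + 0.080)/√(1.16 × 1.04) = −0.20 |
| 0 | −0.304/√1.16 = −0.28 |
| +0.5 | (−0.304 − 0.080)/√(1.16 × 1.04) = −0.35 |
| +1 | (−0.304 − 0.160)/√(1.16 × 1.16) = −0.40 |

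The loss can be large, small or absent, depending on how ICU-onset patients differ in ARI. The document does not say.

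**The case against.** The best defence is that the lead-in about admission is loose. The list under it includes a collection-day dose and blood gases around the protocol, which cannot be ICU-admission values for later-onset patients. Together with the single-occasion statement and the Table 2 row, one could argue that a session SOFA was intended. This part stands: the timing is inconsistent, not uniformly wrong. It does not remove the point, because SOFA alone in that list carries an explicit ICU-admission tag and nothing in the article overrides it.

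A reader might infer that all the severity markers are out of date. The text does not support that. Vasoactive dose is taken on the collection day and brain dysfunction is assessed at data collection. Lactate and CAM-ICU sit under the loose lead-in without an ICU-admission tag of their own, so they need clarifying but are not shown to be mistimed.

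A reader might also infer that ICU-onset patients necessarily score too low and that a real association would probably be missed. Neither follows. Such patients may have had a high SOFA on admission for another reason, and step 4 shows that a systematic offset need not shrink the correlation.

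Finally, the analysis is one marker within one of four secondary objectives, declared exploratory, in a pilot. Small numbers limit it in any case: with ideal timing and a true correlation of 0.30, power is 0.47.

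**Conclusion.** The point holds for SOFA. As written, the score correlated with autoregulation may predate the shock in patients already in the ICU, with no upper limit on the gap; for those admitted in shock the gap is at most about 48 hours. Three places in the article also disagree on when SOFA is taken.

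Some blurring, and probably some weakening, of the correlation is to be expected. The fall in power from 0.73 to 0.52 or 0.32 is illustrative: it rests on an assumed true correlation of 0.40, assumed agreement of 0.8 or 0.6 between the two scores, and 40 patients. The share of ICU-onset patients, the agreement between scores and any difference in ARI between the groups are not in the document, so neither size nor direction is established. The primary comparison across MAP targets does not use SOFA and is unaffected. The change is worth making because it is cheap, not because the trial's main result is at risk.

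**What to change.** In Data collection and management and in Table 2, state that the SOFA used for objective 3 is scored on the day of the TCD/B4C recording, from the nearest values before T0 and after shock onset. Vasoactive dose is already tied to the collection day. Keep ICU-admission SOFA for baseline description only. State that lactate and CAM-ICU for this objective are also the values nearest the session; brain dysfunction needs no change. Align the single-occasion statement in the retention section, and the Table 2 column heading, with the noradrenaline-start clock in Table 1.

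The cost is a short amendment and a few extra case report form fields. The values come from routine ICU charting, so they should also be recoverable for patients already enrolled.

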**Methods:**

Prospective, non-randomized, single-center trial, which will study cerebral hemodynamics in patients with septic shock within 48 hours of its onset. Patients will be studied at their baseline MAP and at three MAP targets (T1: 65, T2: 75, T3: 85 mmHg). Cerebral hemodynamics will be assessed by transcranial Doppler (TCD) and a skull micro-deformation sensor (B4C). Dynamic CA will be expressed by the autoregulation index (ARI), calculated by transfer function analysis, using fluctuations of MAP as input and corresponding oscillations in cerebral blood velocity (CBv). The instantaneous relationship between arterial blood pressure and CBv will be used to estimate CrCP and resistance-area product (RAP) for each cardiac cycle using the first harmonic method. The B4C will access ICC by intracranial pressure waveforms (P2/P1). The primary aim is to assess cerebral hemodynamics (ARI, CrCP, RAP, and P2/P1) at different targets of MAP in septic shock patients. Our secondary objective is to assess cerebral hemodynamics at 65mmHg (target recommended by guidelines). In addition, we will assess the correlation between markers of organ dysfunction (such as lactate levels, vasoactive drugs usage, SOFA score, and delirium) and CA.

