### Concealment mechanism

Given the population to be studied, the absence of a control group or the use of placebo, means that concealment is not appropriate for the study.

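### One fixed ascending order (65, 75, 85 mmHg) aliases MAP target with elapsed time over T1–T3, so the primary comparison shows the response to the sequence, not the isolated effect of MAP level

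*Protocol article*

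**What the plan says.** All references are to the Protocol article.

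- **Order.** Methods: Data collection and management sets a single sequence for all patients once baseline has been recorded: "the mean arterial pressure (MAP) targets will be sequentially increased in the order of 65, 75, and then 85 mmHg". The only reason given is "This structured approach ensures sample homogeneity".
- **Control.** Concealment mechanism: "the absence of a control group or the use of placebo, means that concealment is not appropriate for the study". The article describes no return to an earlier target and no repeat recording at one pressure.
- **Timing.** The chronology table under Recruitment gives "Intervention protocol (5 min on each MAP target". The time needed to reach and settle at each target is not stated.
- **Baseline.** Abstract, Methods: "Patients will be studied at their baseline MAP and at three MAP targets (T1: 65, T2: 75, T3: 85 mmHg".
- **Analysis.** Statistical methods: Outcomes compares "T1 (65 mmHg), T2 (75 mmHg), and T3 (85 mmHg) using a two-way repeated-measures ANOVA". The second factor of the ANOVA is not named. Mixed models on the pressure targets are only to be considered, and no time or period term is mentioned.
- **Interpretation.** Objectives and Study outcome read the comparison as the effect of MAP target on ARI, CrCP, RAP and P2/P1.

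**The concern.** The trial asks whether the level of MAP changes cerebral hemodynamics. In every patient the higher target is also the later one. Anything that changes with time during the session therefore moves with the target: cumulative vasopressor exposure, carbon dioxide, depth of sedation, sensor or probe position. A pure time trend would be reported as a MAP effect, and a trend in the other direction would hide a real one.

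The homogeneity argument does not answer this. Giving every patient the same order does not remove an order effect. It makes the effect common to all patients, which is exactly the form that passes undiluted into a within-patient contrast. The consequence goes beyond this study, because the Sample size section says that the results will be used to size later trials.

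**Working it through.** The plan states no power, effect size or SD, so there is no figure of its own to reproduce.

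**Inputs from the article:** n = 40 (the stated minimum), stages T0–T3, targets 65/75/85 in fixed order, alpha 0.05. **Assumed:** drift per stage *d* in units of the within-patient residual SD, baseline MAP normal with mean m and SD s, targets hit exactly.

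**1. Aliasing.** The correlation of target (65, 75, 85) with order (1, 2, 3) is exactly 1. A design matrix with patient, target and period has rank 42 of 44 columns for T1–T3. For T0–T3 as labelled levels it has rank 43 of 46. With patients and an intercept-equivalent accounted for, no target contrast is estimable separately from period.

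**2. False target effects with no MAP effect.** For a one-factor repeated-measures ANOVA with k levels and linear drift, the noncentrality is λ = n·d²·Σ(j − j̄)².

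- T0–T3: Σ = 5, so λ = 200d², with 3 and 117 df.
- T1–T3: Σ = 2, so λ = 80d², with 2 and 78 df.

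| Drift per stage (SD) | λ, T0–T3 | Rejection, T0–T3 | λ, T1–T3 | Rejection, T1–T3 |
|---|---|---|---|---|
| 0 | 0 | 5% | 0 | 5% |
| 0.10 | 2.0 | 19% | 0.8 | 11% |
| 0.15 | 4.5 | 39% | 1.8 | 20% |
| 0.20 | 8.0 | 64% | 3.2 | 33% |
| 0.30 | 18.0 | 95% | 7.2 | 65% |

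Simulations agree within Monte Carlo error: for 0.15 and 0.30 on four levels, about 37–39% and 95–96%.

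**3. Masking.** Suppose a true slope of 0.02 ARI points per mmHg and a drift of −0.2 points per stage. Then T3 − T1 = 0.02 × 20 − 0.2 × 2 = 0.

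**4. What baseline can contribute.** T0 is taken at the patient's own MAP, so it need not lie on the ascending line. Write δ = m − 75. The mean within-patient sum of squares of MAP is S = 200 + 0.75(δ² + s²).

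- Linear period term: r² = (20 − 1.5δ)² / (5S), and the slope SE is multiplied by 1/√(1 − r²).
- Four-level period: the share of MAP information left is f = 0.75s²/S, and the SE is multiplied by 1/√f.

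| Baseline MAP (mean, SD) | S | r² | SE rise, linear | f | SE rise, four-level |
|---|---|---|---|---|---|
| 65, 3 | 281.8 | 0.870 | +177% | 2.4% | +546% |
| 65, 6 | 302.0 | 0.811 | +130% | 8.9% | +234% |
| 70, 6 | 245.8 | 0.615 | +61% | 11.0% | +202% |
| 75, 8 | 248.0 | 0.323 | +21% | 19.4% | +127% |
| 75, 10 | 275.0 | 0.291 | +19% | 27.3% | +91% |
| 80, 10 | 293.8 | 0.106 | +6% | 25.5% | +98% |

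In the four-level version all the information comes from the spread of baseline MAP (f = 0 when s = 0), and none from the 65/75/85 comparison.

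**5. Does a linear period term restore the error rate?** Simulation with no MAP effect, baseline mean 75, SD 8, n = 40:

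| Drift at T0, T1, T2, T3 (SD) | Measured MAP alone | MAP + linear period | MAP + four-level period |
|---|---|---|---|
| 0, 0.3, 0.6, 0.9 (linear) | 62% | 5% | 5% |
| 0, 0.6, 0.6, 0.6 (shift after baseline) | 5% | 41% | 5% |
| 0, 0, 0.3, 0.9 (late drift) | 93% | about 30% | 6% |

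The linear term protects only if the drift is linear. The four-level version holds for any common drift shape, at the SE cost shown in step 4.

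**The case against.** **No drift is shown.** The article reports no drift, recordings last 5 minutes, the probe is held in a helmet frame on one side throughout, and signal quality is watched. This stands. The drift sizes above are illustrations, and a reader who infers that the trial's MAP effect will be spurious goes beyond the documents. What the documents establish is that the design could not reveal drift within T1–T3 if it occurred.

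**Vasopressor dose is part of the intervention.** A dose that rises with the target would do so in any order, so only cumulative exposure is an order effect. This also stands.

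**The model may be settled elsewhere.** The second ANOVA factor is undefined, mixed models are left open, and a fuller analysis plan may exist. That is a reason not to fault the missing period term as such. It does not rescue the T1–T3 contrast, because the order is fixed by design and no analysis by target label can separate target from period.

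**A stronger remedy is tempting.** A reader might infer that making measured MAP plus a period term the primary model, with end-tidal CO2 at each stage, would solve the problem. The material does not support that. The 5% error rate needs linear drift, the separation depends on one uncontrolled baseline recording, and CO2 is not stated to be recorded at each stage: capnography may be unavailable, and blood gases are taken only before and after the protocol.

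**Varying the order** would break the aliasing, but it removes the confounding only if there is no carry-over between steps. A fixed ascending order may also have a safety reason, although the article states none.

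**Conclusion.** The point holds as a limit on interpretation. Over T1–T3, and over T0–T3 as labelled levels, target and elapsed time are completely aliased, and the uniform order does not protect against this. That part needs no assumption. Its possible size does. With 40 patients and no MAP effect, linear drift of 0.15 to 0.30 SD per stage would give a significant four-level test in about 39% to 95–96% of trials.

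It would go too far to say that pressure and time cannot be separated at all. Baseline at the patient's own MAP allows measured MAP and period to be estimated together. That separation is weak, however. It requires a linear MAP response, drift unrelated to a patient's baseline MAP, and, in the linear-period version, linear drift as well. It suits a sensitivity analysis, not the primary one.

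**What to change.** 1. In Methods: Data collection and management, delete the homogeneity sentence. In Objectives and Study outcome, state that differences across T1–T3 are the response to a stepwise ascending sequence (pressure plus elapsed time) and not the isolated effect of MAP level.
2. In Statistical methods: Outcomes, keep the planned primary analysis. Add a pre-specified sensitivity mixed model for each parameter with measured MAP and recording number (0–3), fitted once with recording number linear and once as four-level period. State that separation rests entirely on the baseline recording, and that the linear version is valid only if both drift and MAP response are linear.
3. Describe end-tidal CO2 by stage where capnography exists, without making it a required covariate.

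Whether another order is clinically acceptable is for the investigators, and none of these changes depends on it.

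The cost is wording and one additional model, with no new patients or procedures. The downside is that the sensitivity slope will be imprecise. For assumed mean baseline MAP of 65–80 mmHg, its SE rises by about 5% to 180% with linear period. With four-level period it roughly doubles at best, and rises far more if baseline MAP varies little between patients.

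### With 5-minute recordings, 102.4 s segments at 50% overlap yield only four segments and leave the last 44 s out of the ARI estimate; a slightly larger overlap would give five

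*Protocol article*

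**What the plan says.** All the settings stand in the protocol article, under Methods: Data collection and management.

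- Recording length: dynamic autoregulation is estimated from "recordings for each MAP target (lasting 5 min" minutes as stated there). Table 2, under Recruitment, agrees: "Intervention protocol (5 min on each MAP target").
- Baseline: "Baseline cerebral hemodynamic parameters will be reported as the average over a 5-min recording at rest".
- Sampling: "Beat-to-beat data will be spline interpolated and resampled at 5 Hz".
- Spectral smoothing: Welch's method with "102.4 s segments, 50% superposition", which produces coherence, gain and phase.
- ARI: "Using the inverse fast Fourier transform, the CBv response to a step change in MAP will also be derived" and then matched to template curves. An ARI below 4 defines impaired autoregulation.

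The article gives no segment count and names no window.

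**The concern.** Welch's method averages spectra over segments, and the noise in the average falls as segments are added. Here the recording length and the segmentation do not fit each other: the recording ends just before a fifth segment would be complete, so the final part goes unused in this step.

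ARI is one of the four components of the primary outcome. It also defines impaired autoregulation and enters the correlations with organ dysfunction. Each patient contributes one ARI per pressure level, and the planned minimum is 40 patients. Avoidable estimation noise in ARI therefore makes the T0 to T3 comparison less precise, causes some misclassification around the cut-off of 4, and weakens correlations. The loss is one of precision. The same segmentation applies at every level, so nothing here points to bias between targets.

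**Working it through.** **Inputs from the article.** Recording 5 min = 300 s; 5 Hz; segment 102.4 s; overlap 50%. The article states no segment count, so there is no figure of its own to reproduce.

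**In samples.**
- Recording: L = 300 × 5 = 1500
- Segment: n = 102.4 × 5 = 512
- Step at 50% overlap: h = 256 (51.2 s)

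**Segments that fit.** K = floor((L − n)/h) + 1 = floor(988/256) + 1 = floor(3.86) + 1 = 4.

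**Data used.** n + (K − 1)h = 512 + 3 × 256 = 1280 samples = 256 s. Unused: 300 − 256 = 44 s, and 44/300 = 14.7%.

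**Length needed for five at 50%.** 102.4 + 4 × 51.2 = 307.2 s, a shortfall of 7.2 s. Any recording from 256 s to just under 307.2 s gives four segments.

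**Five segments within 300 s.** Step = (1500 − 512)/4 = 247 samples (49.4 s). Overlap = 1 − 247/512 = 51.8%. Starts are 0, 247, 494, 741 and 988, and the last segment ends at 988 + 512 = 1500.

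**Effect on the spectral estimates.** Relative to a single segment, the variance of the average is

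V = (1/K) × [1 + 2 Σ (1 − m/K) ρ_m²],

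where ρ_m is the correlation of the window with itself shifted by m steps. The window is assumed, so two choices are shown.

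- Rectangular, four segments at 50%: ρ₁ = 0.5, V = 0.25 × (1 + 2 × 0.75 × 0.25) = 0.344.
- Rectangular, five segments at step 247: ρ₁ = 265/512 = 0.518, ρ₂ = 18/512 = 0.035, V = 0.2 × [1 + 2 × (0.8 × 0.268 + 0.6 × 0.001)] = 0.286. Ratio 0.286/0.344 = 0.83.
- Hann, four segments at 50%: ρ₁ = 1/6, V = 0.25 × (1 + 2 × 0.75 × 0.0278) = 0.260.
- Hann, five segments at step 247: V = 0.212 (4.72 effective segments against 3.84). Ratio 0.212/0.260 = 0.81.

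The variance therefore falls by 17% to 19%. In standard deviation, √0.83 = 0.91 and √0.81 = 0.90, a fall of about 9% to 10%.

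**Effect on ARI.** This depends on the template fit and has no simple formula. A simulation used 300 s at 5 Hz, a Hann window, true ARI of 3, 5 or 6, and noise SD 0.7 to 1.5 times the signal SD. Template parameters, band limits and noise levels were all assumed. Five segments at step 247 lowered the variance of ARI by 12% to 24% against four (for example, SD 1.28 to 1.13 at a true ARI of 3). Misclassification at the cut-off of 4 fell by 1 to 4 percentage points in eight of nine settings and was unchanged in the ninth. A second simulation, again with assumed templates and noise, gave about 12% to 27%. When the templates were not band-limited like the data, the true ARI was not recovered and there was little or no gain at ARI 5 to 6. These figures indicate the order of the effect only.

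**The case against.** The strongest reply is that nothing in the plan is wrong. Four 102.4 s segments fit into 5 minutes, they yield an ARI, and the article claims no other count. It also refers to earlier publications for the method, and the 5 minutes and 50% may be nominal: 2.4% more recording (7.2/300) or 1.8 points more overlap would produce the fifth segment. The study is a pilot without a power calculation, and the added noise is the same at all levels.

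Much of this stands. The point is about efficiency, and it depends on the settings being applied as printed. It remains worth raising because the recording length, segment length and overlap are all stated rather than left open, and together they waste data that will already have been collected.

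A reader might infer more than the document supports:

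- *That the plan contains an arithmetic error or contradiction.* It does not, since no segment count is stated.
- *That 44 s of every recording is thrown away.* Only the transfer-function step omits it. CrCP and RAP are computed for each cardiac cycle, P2/P1 comes from the B4C curve without Welch segmentation, and baseline parameters are averaged over the whole recording.
- *That many recordings will have unreliable transfer functions.* Chance coherence is higher with four segments: its simulated 95% point is 0.64 to 0.73, against about 0.55 to 0.65 with five at step 247. The article states no coherence threshold, however, so no number of failing recordings can be derived.
- *That recordings should be lengthened.* This would change the time at each induced pressure target, which Table 2 sets as part of the intervention. It is not proposed, and the full gain from 307.2 s (a 20% fall in variance with a Hann window) is not claimed.

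**Conclusion.** The point holds as an inefficient specification. If recordings last 300 s and the overlap is exactly 50%, each transfer function, and so each ARI, rests on four segments and 256 s of data. Five could be had from the same recording.

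The cost is about a sixth to a fifth of the variance of the averaged spectral estimates, depending on the window, which the article does not name. The gain in ARI appears to be of similar size under assumed noise and templates, but this is less certain. CrCP, RAP and P2/P1 are not involved. The planned ARI analysis remains usable without the change. The change is worth making because it improves a component of the primary outcome at almost no cost.

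**What to change.** Keep the 5-minute recording and the 102.4 s segment. Set the step to 247 samples (51.8% overlap; starts 0, 247, 494, 741, 988), identically at T0, T1, T2 and T3, and state that five segments are averaged.

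This step leaves no slack. A usable record of 299 s (1495 samples) would again give floor((1495 − 512)/247) + 1 = floor(3.98) + 1 = 4. It is therefore safer to fix the count at five and let the step follow as floor((N − 512)/4) for a record of N samples. At N = 1500 this is 247. At N = 1495 it is 245, an overlap of 1 − 245/512 = 52.1%. The count then stays the same across levels when records differ by a few seconds.

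The cost is one setting in the off-line analysis and a slight departure from the nominal 50% overlap. The segment length, and hence the frequency resolution, is unchanged, as is the time at each MAP target. The protocol computes the derived parameters after data collection, so the setting can still be fixed before the analysis.
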